## Abstract

**Background:**

Abdominal obesity and presence of the metabolic syndrome (MetS) significantly increase the risk of developing diseases such as Type 2 diabetes mellitus (T2DM) with escalating emergence of MetS and T2DM constituting a significant public health crisis worldwide. Lower prevalence of inflammatory and metabolic diseases such as T2DM in countries with higher incidences of helminth infections suggested a potential role for these parasites in the prevention and management of certain diseases. Recent studies confirmed the potential protective nature of helminth infection against MetS and T2DM via immunomodulation or, potentially, alteration of the intestinal microbiota. This Phase 1b safety and tolerability trial aims to assess the effect of inoculation with helminths on physical and metabolic parameters, immune responses, and the microbiome in otherwise healthy women and men.

**Methods:**

Participants eligible for inclusion are adults aged 18–50 with central obesity and a minimum of one additional feature of MetS recruited from the local community with a recruitment target of 54. In a randomised, double-blind, placebo-controlled design, three groups will receive either 20 or 40 stage three larvae of the human hookworm *Necator americanus* or a placebo. Eligible participants will provide blood and faecal samples at their baseline and 6-monthly assessment visits for a total of 24 months with an optional extension to 36 months. During each scheduled visit, participants will also undergo a full physical examination and complete diet (PREDIMED), physical activity, and patient health (PHQ-9) questionnaires. Outcome measurements include tolerability and safety of infection with *Necator americanus*, changes in metabolic and immunological parameters, and changes in the composition of the faecal microbiome.

**Discussion:**

Rising cost of healthcare associated with obesity-induced metabolic diseases urgently calls for new approaches in disease prevention. Findings from this trial will provide valuable information regarding the potential mechanisms by which hookworms, potentially via alterations in the microbiota, may positively influence metabolic health.

**Trial registration:**

The protocol was registered on ANZCTR.org.au on 05 June 2017 with identifier ACTRN12617000818336.

Alternatively, a Google search using the above trial registration number will yield a direct link to the trial protocol within the ANZCTR website.

## Background

Since 1980, numbers of obese or overweight adults and children have grown exponentially worldwide to a current estimate of 2.1 billion people, thus establishing obesity as a pandemic and the fourth leading cause of death worldwide in 2017 [1]. Specifically, abdominal obesity has been highlighted as the central factor in metabolic syndrome (MetS), a cluster of physiological, metabolic, and biochemical risk factors including abdominal obesity, insulin resistance, hypertension, and dyslipidaemia, as it appears to precede all other factors [2]. Presence of MetS significantly increases the risk of developing several life-threatening diseases such as cancer, cardiovascular disease (CVD), and Type 2 diabetes mellitus (T2DM) [2]. With almost one quarter of the world’s population affected, the prevalence of MetS in adults in rural Australia alone is 35.8%, and numbers in the Asia-Pacific region are growing disproportionately [3], likely due to rapid socio-economic development and adoption of the Western diet and sedentary lifestyle [4]. Associated with MetS, the escalating emergence of non-communicable diseases such as CVD and T2DM constitutes a significant public health crisis for the affected regions [3].

Central and visceral obesity observed in MetS are a strong predictor for the development of T2DM, as they promote chronic inflammation and subsequent insulin resistance [5]. Worldwide numbers of patients with T2DM are on the rise, and currently 8.8% of adults are living with the disease, equating to 425 million people (http://www.diabetesatlas.org). Although the causative mechanisms are not exhaustively understood, chronic inflammation is increasingly accepted as strongly implicated in the pathogenesis of T2DM as excess calorie intake and sedentary behaviour are in the development of obesity [6]. Vascular dysfunction resulting from chronic inflammation enhances the risk of diabetic complications such as myocardial infarction, peripheral arterial disease, and diabetic nephropathy and retinopathy [7].

Interestingly, increasing incidence and prevalence of inflammatory diseases such as T2DM, inflammatory bowel disease, and asthma in developed countries offset the successful reduction in parasite-related diseases following helminth eradication efforts [8]. In 1989, the lower prevalence of inflammatory diseases in transitioning or low-middle income countries with higher incidences of helminth infections [9] led to development of the “Hygiene Hypothesis” and generated suggestions of a potential role for symbiotic parasites in the prevention and management of certain inflammatory diseases [10]. Data from cross-sectional and animal studies further corroborate this inverse relationship between helminths and inflammatory diseases. A cross-sectional study in Northern Australia unearthed an inverse relationship between infection with *Strongyloides stercoralis* and T2DM, indicating a possible protective relationship [11]. A recent meta-analysis also confirmed a potential protective nature of helminth infection against T2DM [10] with another study indicating an inverse relationship between helminth infection and CVD risk factors such as dyslipidaemia [10]. Further supporting this notion, a recent study in a helminth-endemic region of Indonesia showed that anthelminthic drug treatment of people with an active helminth infection significantly raised HOMA-IR values and insulin resistance, suggesting that the removal of worms was causally associated with worsened glycaemic control [12]. Findings from animal studies confirm the suggestion of a possible protective effect of helminth infections against T2DM and MetS via processes of immunomodulation [9], where helminth infections may dampen pro-inflammatory immune responses and skew towards a type 2 immune response [9]. A further study also demonstrated that infection with doses of 20 human hookworm *Necator americanus* (*Na*) is safe, well tolerated, and associated with Th2 and concomitant regulatory T cell responses [13, 14], identifying *Na* as a potentially effective treatment for inflammation associated with MetS and T2DM. Additionally, helminth infections may also modulate immune responses indirectly via their effect on the composition of the intestinal microbiota [15]. For example, infection of mice with gastrointestinal helminths was able to prevent colonisation with the pro-inflammatory bacterium *Bacteroides vulgatus* by inducing a Th2 and regulatory immune response that promoted the expansion of protective *Clostridiales* strains [16]. Finally, a recent review of helminths and T2DM concluded that chronic helminth infections influence the development of metabolic diseases and that these effects can be long lasting; however, human studies to date have been cross-sectional and cannot infer causality [17]. The authors called for controlled human helminth infection trials to better understand how these can modulate the immune and metabolic response.

Herein we describe a randomised, double-blind, placebo-controlled Phase 1b safety and tolerability trial that will assess the effect of inoculation with 20 or 40 infective stage three larvae (L3) of *Na* on body fat composition, inflammation and immune response, in otherwise healthy women and men aged 18–50 with central obesity and features of MetS over 24 months (Table 1).

**Table 1 Tab1:** World Health Organisation Trial Registration Data Set

Data category	Information
Primary registry and trial identifying number	anzctr.org.au (ACTRN1261700818336)
Date of registration in primary registry	05/06/2017
Secondary identifying numbers	N/A
Source(s) of monetary or material support	Far North Queensland Hospital Foundation, Australian Institue of Tropical Health and Medicine
Primary sponsor	James Cook University
Secondary sponsor(s)	None
Contact for public queries	[name] [contact]
Contact for scientific queries	[name], Australian Institute of Tropical Health and Medicine, Cairns, Australia
Public title	Safety and tolerability of experimental hookworm infection in humans with metabolic disease
Scientific title	Safety and tolerability of experimental hookworm infection in humans with metabolic disease: Proof of Concept (Phase 1b) clinical trial
Countries of recruitment	Australia
Health condition(s) or problem(s) studied	Diabetes, Infection
Intervention(s)	Active comparator: 20 or 40 larvae of the human hookworm *Necator americanus* (20 L3, 40 L3) over 24 months.
	Placebo comparator: Tabasco sauce solution
Key inclusion and exclusion criteria	Ages eligible for study: 18–50 years; Sexes eligible for study: both; Accepts healthy volunteers: no
	Inclusion criteria: Healthy adults 18–50 years, with central obesity (WC > 90 cm for females and > 102 cm for males) and increased insulin resistance as assessed via abnormal homeostatic model assessment of insulin resistance (HOMA-IR), i.e. HOMA-IR > 2.12 or at least two other features of MetS: elevated blood pressure > 135/85 mmHg, dyslipidaemia, or abnormal liver function test suggesting fatty liver disease. Have provided written informed consent and are willing to comply with all Protocol scheduled visits. If of childbearing potential, must be willing to use the acceptable methods of contraception.
	Exclusion criteria: Pregnancy, established chronic disease (CVD, diabetes, cancer, renal, gut disorder), history of substance abuse or current substance abuse, major allergies, known immunodeficiency disorder, asthma, taking prescribed medications or nutritional supplements likely to interfere with study outcomes, inability to provide informed consent.
Study type	Interventional
	Allocation: block randomised; intervention model: parallel assignment; Masking: double-blind, sealed envelopes and containers
	Primary purpose: prevention
	Phase 1
Date of first enrolment	March 2018
Target sample size	45
Recruitment status	Recruiting
Primary outcome(s)	Safety of experimental inoculation with 20 L3, defined by (a) Number of reported adverse events (AEs), relative to placebo cohort, (b) Assessment of general health and (c) Successful completion of 24-month trial. Adverse reactions: including but not limited to abdominal pain, rash, fever, weight loss, fatigue, nausea (mild, moderate or severe as assessed by trial doctor).
Key secondary outcome(s)	Changes in insulin sensitivity from blood pathology taken at each participant contact point during the 24-month trial; Change in BMI measured by any alteration in weight (kg) and height (cm); Change in waist circumference (cm) Change in bacterial richness of microbiome measure by shotgun assay of faecal sample

Hypotheses are that experimental infection with the human hookworm *Na*
will be well-tolerated and safe in this cohort of otherwise healthy but obese women and men.will induce a biased Type 2 and regulatory immune response with concomitant suppression of systemic, pro-inflammatory Type 1 responses.will stabilise or improve determinants of metabolic disease.will modify the composition of the gut microbiota.

## Methods/design

### Study design

#### Aims

The aims of this study are
to establish the acceptability, safety, and tolerability of experimental infection with *Na* in obese women and men with features of MetSto conduct exploratory studies into the impact of hookworms on stabilising or improving metabolic, immune/inflammatory, and microbiological parameters associated with metabolic disease

#### Design

This study is designed as a randomised, double-blind, placebo-controlled Phase 1b safety and tolerability trial. An initial recruitment target of 54 allows for a drop-out rate of 20%, leaving 45 volunteers to participate in the trial. Volunteers who meet the eligibility criteria, have been approved following screening, and have given informed consent (Additional file 1) will be randomised into three trial groups. Groups 1 and 2 will be inoculated with either 20 (2 × 10, *n* = 15) or 40 (2 × 20, *n* = 15) L3 of *Na* with Group 3 (Placebo, *n* = 15) administered Tabasco® sauce in a solution identical in appearance to the L3 solutions. All groups will be monitored over a period of at least 24 months followed by an optional extension to 36 months to assess the impact of eliminating the worm infection following anti-worm medication (Fig. 1).

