#### Sample size

This Phase 1b safety and dose-ranging study will include 45 participants with 15 to be infected with 20 x L3, 15 to be infected with 40 x L3, and 15 in the placebo control group. In the absence of other effect size data from human trials upon which to base a power calculation, and as a change in HOMA-IR from Baseline is a primary metabolic outcome of this study, we have adapted the SUGARSPIN HOMA-IR result [29] and assume an effect size of 1.06 over 2 years. A total of 15 participants in each group reflects 80% power to detect an effect size of 1.06 using the T-statistic and 1.023 using Z-statistic. The aim to recruit 54 participants allows for a potential drop-out rate of 20%.

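### Recruiting 54 does not leave 45 after a 20% drop-out, and the plan does not settle whether 45 is the number entering the trial or the number evaluable at 24 months

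*Protocol article*

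**What the plan says.** The Design section gives the starting number, the drop-out rate and the result in one sentence: "An initial recruitment target of 54 allows for a drop-out rate of 20%, leaving 45 volunteers to participate in the trial". The Sample size section repeats the first two: "The aim to recruit 54 participants allows for a potential drop-out rate of 20"%.

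The number 45, or 15 per arm, appears in several roles:

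- Design, as the number inoculated: "Groups 1 and 2 will be inoculated with either 20 (2 × 10, *n* = 15"), with 15 also given for the 40 L3 group and for placebo.
- Sample size, as the number included and infected: "This Phase 1b safety and dose-ranging study will include 45 participants with 15 to be infected with 20 x L3", with 15 in each of the other two groups.
- Table 1, as the registered target: "Target sample size 45".
- Sample size, as the basis for power: "A total of 15 participants in each group reflects 80% power to detect an effect size of 1.06 using the T-statistic", with 1.023 given for the Z-statistic. The same section says the authors "assume an effect size of 1.06 over 2 years", and names change in HOMA-IR from baseline as the endpoint.

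The Abstract gives 54 as the recruitment target. The randomisation section gives a block size of 6.

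**The concern.** There are two linked problems.

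The first is arithmetic. The stated rate, applied to the stated start, does not give the stated result. The drop-out the plan can absorb while keeping 45 is therefore smaller than it claims.

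The second is the meaning of 45. A power figure for an effect over 2 years needs 15 per arm with data at 24 months. Taken literally, the Design section removes the drop-outs before participation and then inoculates 15 per arm. On that reading the plan states no margin for losses during the 24 months after inoculation. On the more usual reading, 54 are randomised and 45 are expected to be evaluable. The text supports parts of both.

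At stake are the accuracy of the stated power for HOMA-IR, and a clear statement of how many people are randomised.

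**Working it through.** **Inputs from the article.** Recruitment target 54, drop-out 20%, number left 45 (Design; Sample size). 15 per arm, 80% power, effect size 1.06 by t and 1.023 by z (Sample size). Block size 6 (randomisation section).

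**Assumption.** The article states neither alpha nor sidedness. I take a two-sided 5% test comparing two arms, with the effect in SD units.

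**Step 1: reproduce the power statement.**

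- By z, the difference detectable with 80% power is (1.960 + 0.842) × √(2/15) = 2.802 × 0.3651 = 1.023. This matches.
- By t (noncentral t, 28 degrees of freedom), the detectable difference at 15 per arm is 1.0598, which rounds to 1.06. Power at exactly 1.06 is 80.0%. This matches.
- A one-sided 5% test would give 88% at 1.06 with 15 per arm, so it does not reproduce the statement.

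The power statement is therefore right for 15 evaluable per arm, and both effect sizes behave as standardised differences solved from n = 15.

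**Step 2: check the recruitment figure.**

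- Number left at 20% loss: 54 × (1 − 0.20) = 43.2, not 45.
- Loss implied by 54 to 45: 1 − 45/54 = 16.7%.
- Number needed to keep 45 at 20% loss: 45/(1 − 0.20) = 56.25, so 57.
- Source of 54: 45 × 1.20 = 54. The target was multiplied by 1 + rate where it should have been divided by 1 − rate.

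**Step 3: power at 1.06 SD under each reading.** The noncentrality is 1.06 × √(n/2), with 2n − 2 degrees of freedom.

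| Situation at 24 months | n per arm | Noncentrality | Power |
|---|---|---|---|
| 45 evaluable | 15 | 2.903 | 80.0% |
| 54 randomised, 20% lost | 43.2/3 = 14.4 | 2.844 | 78.3% |
| Same, rounded down | 14 | 2.805 | 77.0% |
| 45 inoculated, 20% of those lost | 36/3 = 12 | 2.596 | 69.9% |

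The difference detectable with 80% power (t) is 1.06 SD at 15 per arm, 1.10 at 14 and 1.20 at 12.

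**Step 4: block size.** 54/6 = 9 full blocks; 45/6 = 7.5. This fits 54 as the number randomised, but the article does not say so.

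**The case against.** The strongest case on the other side accepts the slip but holds that little follows from it.

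- *The usual reading is benign.* The Sample size section gives 15 per group for power and then 54 to cover drop-out, which is the ordinary evaluable-versus-recruited form, and 54 fills whole blocks. The shortfall is then about two participants and 2 to 3 points of power. This stands, and it limits the size of the point.
- *The power concerns a secondary outcome.* The Outcomes section lists HOMA-IR as secondary, the Aims call the metabolic work exploratory, and formal tests on metabolic parameters are conditional on sample size. The primary outcome is safety of 20 L3, for which no power is claimed. This stands, although HOMA-IR is the only basis the article gives for its sample size.
- *The 70% figure needs a second loss.* It takes 54 down to 45 before inoculation and then removes a further 20%. The article states only one allowance. This stands, so 70% is a conditional figure.

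Three stronger readings are tempting, and the document supports none of them. A reader might infer that 80% power is simply not delivered; it is, if 15 per arm are evaluable at 24 months. A reader might suppose that 1.06 is in raw HOMA-IR units, so that power depends on an unstated SD; but 1.06 and 1.023 both reproduce as standardised differences at 15 per arm. A reader might conclude that 1.06 is not a supportable expected effect. The article says it was adapted from a cited trial's HOMA-IR result, and that source is not available here, so this cannot be judged. What can be said is that the pair 1.06 and 1.023 coincides with what 15 per arm can detect under each test statistic.

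What the objection does not remove is the inconsistent sentence itself, or the unresolved role of 45.

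**Conclusion.** The drop-out statement is wrong as written. From 54, a 20% loss leaves about 43, and 45 corresponds to a 16.7% loss. The article also leaves open whether 45 is the number entering or the number evaluable, and the literal text provides no stated cover for loss after inoculation.

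The likely consequence is small: about 77–78% power in place of 80% if 54 are randomised and 20% are lost. It becomes material, at about 70%, only if 45 are inoculated and a fifth of those are then lost. These figures rest on a two-sided 5% two-arm comparison and an effect of 1.06 SD in change in HOMA-IR.

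This is a should-fix point, because the primary safety outcome carries no power claim.

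**What to change.** 1. Correct the drop-out allowance in Design and Sample size. Either state it as 16.7% (54 to 45), or keep 20% and say that about 43 remain, with power of about 78% at 1.06 SD.
2. State whether 45 (15 per arm) is the number randomised or the number evaluable at 24 months, and reconcile Table 1, Design and Sample size with the answer. The sponsor must decide which was meant; it also determines how many people are inoculated, so it should not be inferred from the block size.
3. Describe 1.06 (t) and 1.023 (z) as the minimum standardised differences detectable with 80% power at 15 per arm, and state the alpha and sidedness used.

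The cost is wording, an update to the registered target if the answer to item 2 requires one, and a slightly less favourable stated figure. No recruitment above the planned 54 is needed; 57 would be required only if the sponsor wished to keep both 20% and 45.

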**Fig. 1 Fig1:**
[figure not shown]
Trial design flowchart

#### Setting

Participants will be recruited from the Cairns and Townsville regions in Far North Queensland, Australia. As of June 2016, the regions' estimated populations were 162,000 (www.cairns.qld.gov.au Accessed 15 November 2018) and > 185,000, respectively (http://www.population.net.au/townsville-population Accessed 3 December 2019). The study site is the James Cook University campus, located in Cairns and Townsville. The human hookworm *Na* is not endemic to these metropolitan areas.

### Participant characteristics

Participant recruitment initiatives include advertising in local media, notices around Cairns including the James Cook University (JCU) Cairns campus, student and staff email lists (with permission from the university), and social media.

#### Inclusion criteria

Eligible for inclusion into this study are otherwise healthy women and men in the primary age window for progression to T2DM (18–50 years) [18] with central obesity (waist circumference, WC > 90 cm for women and > 102 cm for men) and increased insulin resistance as assessed via abnormal homeostatic model assessment of insulin resistance (HOMA-IR), i.e. HOMA-IR > 2.12 [19] or at least two other features of MetS: elevated blood pressure (> 135/85 mmHg), dyslipidaemia (elevated total cholesterol triglycerides, LDL or total cholesterol/HDL ratio, low HDL), elevated fasting blood sugar level, or abnormal liver function tests (abnormal alanine transaminase, aspartate transaminase, alkaline phosphatase, albumin and total protein, globulin, bilirubin, and gamma-glutamyl transferase) suggesting fatty liver disease as per pathology report (Fig. 2, Additional file 2). Volunteers must be willing to comply with all protocol scheduled visits and provide written informed consent prior to study entry with the option to withdraw at any time. Women of child bearing potential should agree to use acceptable methods of contraception.

**Fig. 2 Fig2:**
[figure not shown]
Flow diagram of inclusion/exclusion criteria. WC, waist circumference; CVD, cardiovascular disease; GI, gastro-intestinal; HOMA-IR, homeostatic model assessment of insulin resistance; MetS, metabolic syndrome; BP, blood pressure; BSL, blood sugar level

#### Exclusion criteria

Exclusion criteria include pregnancy, established chronic disease (CVD, diabetes, cancer, renal, gastrointestinal disorders), history of substance abuse, current substance abuse, major allergies, known immunodeficiency disorder, unstable asthma requiring significant maintenance treatment, taking oral prescription medications or nutritional supplements likely to interfere with study outcomes, and inability to give informed consent (Fig. 2).

